## Abstract

**Background:**

Lesbian, gay, and bisexual (LGB) men and women represent one of the highest-risk populations for depressive symptomatology and disorders, with young LGB adults being at greatest risk. To date, there have been no randomized controlled trials (RCT) to specifically target depressive symptoms in young LGB adults. This is despite research highlighting unique predictors of depressive symptomatology in this population. Here we outline a protocol for an RCT that will test the preliminary efficacy of a tailored compassion-focused therapy (CFT) intervention for young LGB adults compared with a self-directed cognitive behavioral therapy (CBT) program with no specific tailoring for LGB individuals.

**Methods:**

The CFT intervention consists of 8 units with self-directed reading and activities tailored to LGB young adults, and 8 x weekly 1-hour consultations with a therapist. The CBT intervention consists of 8 units with self-guided reading and activities, with 1 x 1-hour session with a therapist at the mid-point of therapy. Fifty LGB individuals with scores of 13 or above on the Beck Depression Inventory-II will be randomized to either the CFT or CBT condition. The primary outcome measure is depressive symptomatology. Secondary outcome measures are symptoms of anxiety, suicidal ideation, internalized homophobia, self-compassion, and shame and guilt proneness. Assessments will occur at pre-intervention, post-intervention, and at 3-month post-intervention.

**Discussion:**

This study is an RCT to test the preliminary efficacy of an LGB-tailored compassion-focused intervention for young LGB adults with depressive symptomatology. If this intervention is efficacious, this could begin to address the substantial mental health disparities amongst sexual minorities.

**Trial registration:**

ACTRN12616001018404. Prospective registration, registered 02/08/2016.

## Background

A large and coherent body of evidence reveals that LGB individuals experience poorer mental health than their heterosexual counterparts [1, 2]. Meta-analytic reviews indicate that gay men are between two and four times as likely to have attempted suicide, engaged in deliberate self-harm, or experienced depression, compared to their heterosexual counterparts [1]. Similarly, lesbian women are about twice as likely to have experienced depression or attempted suicide compared to heterosexual women [1]. Young LGB individuals are at greatest risk for depressive disorders. Specifically, LGB individuals in their teens and early 20s are more likely to suffer depression than both their heterosexual counterparts [3] and older LGB adults [4]. Suicide in this group is alarmingly high, with meta-analyses showing a 3-fold increase in the odds of suicidal ideation and attempted suicide in those aged younger than 21 years compared to their heterosexual counterparts [3].

These mental health disparities are largely accounted for by the impact of stigma, including internalized stigma or shame [5, 6]. Most LGB individuals report having experienced at least one incident of homophobic harassment, violence, or discrimination [6, 7]. Specifically, meta-analyses indicate that 44% of LGB individuals have been threatened with violence [8], 28% have been physically assaulted [9], and up to 80% have experienced verbal harassment [9]. In a large sample of heterosexuals and LGB individuals, perceived discrimination was related to lower quality of life, and increased indicators of psychiatric morbidity [6]. Importantly, when controlling for the effects of perceived discrimination, there were no differences in psychiatric morbidity between heterosexual and LGB individuals.

Although the risks associated with “coming out” have changed from previous generations for young LGB individuals [10], they still encounter significant life stressors such as family rejection [11] and discrimination [9]. Large numbers of LGB young people also face a range of developmental challenges related to their sexual orientation, such as coming to terms with their sexuality, “coming out” to family and friends, and experiences of discrimination and rejection. Importantly, the highest risk time for suicidal ideation and suicide attempts is when LGB individuals “come out” to their families [12]. To date, there has been no randomized controlled trial specifically designed to treat depression in LGB young adults. This is problematic, as there are unique issues that predict depressive symptomatology in LGB individuals and, in particular, LGB young adults, which interventions need to address. For instance, this population is exposed to a range of stigma-related or *minority stressors* [13], including *internalized* stigma and shame related to one’s sexual orientation, which predicts high risk for depression [14].

Many LGB people who seek help for mental health problems are not successful in getting the help they need [15]. Some report barriers such as a fear of discrimination [16] and lack of LGB sensitivity of services [17] and, of those who do access treatment, many report low satisfaction with treatment [15, 16]. These barriers can be partly overcome when using internet based support [17]. Recent research from our own team demonstrates that mental health interventions need to be tailored to be appropriate for LGB people, as existing interventions are often viewed as not appropriate, relevant, or inclusive of LGB individuals [18, 19]. Our team have also identified preferences that LGB young adults have regarding delivery and content of interventions to enhance efficacy [18, 19], and recently published the world’s first set of guidelines for tailoring therapy to the needs of LGB people [18].

One promising approach to helping LGB people with depression and depressive symtomatology is compassion-focused therapy (CFT). CFT is an evidence-based psychological intervention derived from a range of psychotherapies, and research in evolutionary, social and neuropsychology, along with the comtemplativre traditions [20]. This approach focuses on helping people access and cultivate care-focused motives and emotions to address issues of shame and self-criticism and build supportive inner resources [20]. Much evidence reveals that mindful compassion-based skills lead to a range of beneficial psychosocial outcomes, including increased self-esteem [21], more positive interpersonal relationships [22], and reduced symptoms of depression [23].

Since CFT was originally developed for and with individuals with high shame and self-criticism, it is likely to be particularly beneficial for LGB individuals for at least three reasons: (1) being compassionate predicts well-being in LGB individuals [24]; (2) internalized stigma is a significant predictor of depression in LGB individuals [14], and CFT directly reduces different types of shame and harsh self-criticism [25]; and (3) compassion-based interventions have been shown to be effective in reducing depressive symptoms (*d* = .86) [26], with a recent meta-analysis also reporting significant moderate effect sizes [27]. As mentioned, a significant predictor of mental health among LGB people is internalized stigma, or feelings of shame and low self-worth related to their sexual orientation [14]; indeed, the emphasis on “gay pride” in LGB communities is largely related to combatting and undermining internalized stigma [10]. Coupled with the non-judgemental awareness and mindful sensitivity to distress, CFT fosters sympathy, empathy, and distress engagement with a commitment to develop the wisdom and courage to alleviate and prevent distress. CFT uses concepts from evolutionary theory and research pertaining to the nature of sexuality and other motives and emotions and provides specific practices for emotion regulation, and strategies to switch from hostile self-criticism to compassionate self-support.

### Study objectives and hypotheses

The present RCT will test the preliminary efficacy of a newly developed tailored CFT intervention specifically designed to meet the needs of LGB young adults compared to a standard untailored CBT intervention. The aim is to assess whether a CFT intervention specifically tailored for LGB young adults will reduce depressive symptomatology and shame, and improve psychological functioning.

With regards to the primary outcome, it is hypothesized that, compared to the CBT condition, those in the CFT condition will demonstrate significantly lower symptoms of depression at post-intervention and 3-month follow-up compared to baseline pre-intervention levels. With regard to secondary outcomes, it is hypothesized that compared to those in the CBT condition, those in the CFT condition will demonstrate significantly lower symptoms of anxiety, suicidal ideation, internalized homophobia, and shame and guilt proneness, and significantly higher scores on a measure of self-compassion at post-intervention and 3-month follow-up compared to baseline levels.

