### Study integrity, trial design, and procedure

The present study received ethical approval from the La Trobe University Human Research Ethics Committee (HEC016-10), and the trial was registered with the Australian New Zealand Clinical Trials Registry (ACTRN12616001018404). The present RCT adheres to the CONsolidated Standards Of Reporting Trials (CONSORT). The intervention protocol for both conditions will be manualized, and sessions with therapists for both conditions will be audio-recorded to enable quality assurance and assessment of protocol adherence.

The design will be a RCT involving 50 young adults, recruited over a five-month period (10 participants per month). This sample size was calculated using G*Power software to enable sufficient assessment of change over time in the study outcome measures. To assess change across three time points and between two conditions in a mixed-design ANOVA with both within (time) and between (condition) subjects effects, a sample of 42 is needed to detect a small-medium effect size of *f* = .20 at power = .80 and alpha = .05. Therefore, a sample of 50 will provide sufficient power while also accounting for possible attrition. Analyses will be conducted on an intention to treat basis.

Informed consent will be obtained prior to each participant commencing the study. Following initial screening described above, a research assistant will provide each participant with a pre-intervention questionnaire which will assess the primary and secondary outcome measures described below. Following completion of the pre-intervention questionnaire, participants will be randomly assigned to either the CFT or CBT condition with simple randomization using a computerized random number generator, and will be provided with the respective guidebooks. A therapist will contact participants approximately 1 week later to schedule session appointments. Participants will complete their respective intervention across an 8-week period. One-week post-intervention, a research assistant will provide each participant with a post-intervention questionnaire, which will again assess the primary and secondary outcome measures described below, as well as consumer satisfaction. Three-months post-intervention, the research assistant will provide participants with the follow-up questionnaire containing the primary and secondary outcome measures.

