### Measures

#### Primary outcome

The primary outcomes will be depressive symptomatology, assessed by the Beck Depression Inventory-II (BDI-II) [28]. The BDI-II is a widely used 21-item self-report measure of depressive symptomatology which requires participants to respond to statements describing symptoms of depression on a scale from 0 (*never*) to 3 (*always*). The BDI-II specifies symptom severity from non-clinical to clinical ranges, and has demonstrated sound reliability and validity [32, 33].

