### Statistical analyses

This RCT is a mixed-model repeated measures design involving between- and within-participants factors. The between-participants factor, or independent variable, is condition (CFT vs CBT). The within-participants factor is assessment time, with each participant assessed on relevant primary and secondary outcome measures at three time points (pre- and post-intervention, plus 3-month follow-up). A mixed-model repeated measures analysis of variance (ANOVA) will assess main and interaction effects across the three time points and between the two conditions. Participants in both conditions will also complete the BDI at each session with the therapist (sessions 1–8 for those in the CFT condition, at session 4 for those in the control). Should any participant not complete the post-questionnaire, their most recent BDI score will be used in order to maximize all available data. The effect size (Cohen’s *d*) and its precision will be calculated with 95% CI for the mean differences between pre-, post-, and follow-up for each condition.

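### The planned ANOVA effects and within-condition effect sizes give no CFT–CBT difference at either of the two time points named in the primary hypothesis

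*Protocol article*

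**What the plan says.** The hypothesis (Study objectives and hypotheses) opens as a comparison with the CBT condition and continues that "those in the CFT condition will demonstrate significantly lower symptoms of depression at post-intervention and 3-month follow-up compared to baseline pre-intervention levels". It is therefore a between-arm claim about change from baseline, made at two time points joined by *and*.

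The outcome carries no time point (Primary outcome): "The primary outcomes will be depressive symptomatology, assessed by the Beck Depression Inventory-II (BDI-II").

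The analysis section states that "A mixed-model repeated measures analysis of variance (ANOVA) will assess main and interaction effects across the three time points and between the two conditions". It names none of these effects as decisive and plans no between-arm contrast at a given time. The effect sizes, with 95% confidence intervals, are "for the mean differences between pre-, post-, and follow-up for each condition", which as written are changes within an arm.

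The sample size (Study integrity, trial design, and procedure) is meant "to enable sufficient assessment of change over time in the study outcome measures": "a sample of 42 is needed to detect a small-medium effect size of" f = .20 "at power = .80 and alpha = .05". The F test that this powers is not named.

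**The concern.** The hypothesis asks whether CFT beats CBT at post-intervention and again at 3 months. The mixed ANOVA gives three F tests, and none of them answers that question alone.

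- **Time** compares assessments with the arms pooled, so it is not a treatment comparison.
- **Condition** compares the arms on the average of all three assessments, including the one taken before randomization.
- **Condition by time** does compare change between arms, but over both follow-ups at once and without direction.

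The within-condition effect sizes do not fill the gap. Followed as written, the trial could report a significant interaction and two sets of within-arm changes, and still give no estimate of how much better CFT was than CBT at either time point.

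**Working it through.** **Inputs from the article.** Two conditions, three assessments, f = .20, power .80, alpha .05, N needed 42, N planned 50.

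**Assumptions, not in the article.** Equal variances, one common correlation rho = 0.5 between assessments, sphericity, equal arms, and no dropout at N = 50.

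**1. The stated sample size.** For the interaction, lambda = f² × N × 3/(1 − rho) = 0.04 × 42 × 3/0.5 = 10.08, with 2 and 80 degrees of freedom. Power is 0.803, so 42 reproduces. At N = 50, lambda = 12.0 and power is 0.873. With rho = 0.3 or 0.7 the required N is 58 or 26. The time main effect also gives exactly 42, so the sample size does not show which test was meant. The condition main effect at f = .20 would need 134.

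**2. What f = .20 means.** Let CFT be better by d SD at both follow-ups and equal at baseline. The arm differences (0, d, d) deviate from their mean by −2d/3, d/3 and d/3, with sum of squares 2d²/3. Each arm carries half of each deviation, so f² = (2d²/3)/(4 × 3) = d²/18, and d = 0.20 × √18 = 0.85.

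**3. The interaction does not locate the effect.** If CFT is better at post-intervention only, the differences are (0, d, 0), with deviations −d/3, 2d/3 and −d/3. The sum of squares is again 2d²/3, so lambda and power are the same as for a lasting effect. Simulation (40,000 trials, N = 50, d = 0.85):

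| True pattern | Interaction significant | Both change contrasts significant for CFT |
|---|---|---|
| Equal effect at both times | 87% | 74% |
| Post-intervention only | 87% | 2–3% |

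At N = 42 the first row is 80% and 64%.

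**4. The two main effects.** If both arms improve equally by 0.5 SD, the time effect is significant in 96% of trials at N = 50, with no difference between arms. For the condition effect, a constant follow-up effect d becomes (0 + d + d)/3 = 2d/3. The variance of a three-assessment mean is (1 + 2 × 0.5)/3 = 0.667. At N = 42 the noncentrality is (2 × 0.849/3)/√0.667 × √(42/4) = 2.24, and power is 0.59, against 0.80 for the interaction.

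**5. Baseline-adjusted contrast.** The noncentrality at one time point is d × √(N/4)/√(1 − rho²) = 0.849 × 3.536/0.866 = 3.46 at N = 50, so power is about 92%, against 87% for the interaction. With rho = 0.3 the noncentrality is 3.14 and power 87% (interaction 73%). With rho = 0.7 it is 4.20 and both analyses have about 98%. The two adjusted contrasts correlate at (0.5 − 0.25)/(1 − 0.25) = 1/3. For an equal effect at rho = 0.5, both are significant in about 85–86% of simulated trials, against about 74% with change scores.

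**6. False positives with no arm difference (rho = 0.5).**

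| Rule for success | Chance |
|---|---|
| Interaction only | 5.0% |
| Both change contrasts significant in favour of CFT | about 0.4% |
| Either time-point contrast | 9.1% |
| Condition main effect or interaction | 9.75% |

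**The case against.** The strongest reply is that the interaction is the right test: the hypothesis is a between-arm difference in change from baseline, which is what condition by time examines, and it reproduces N = 42. This largely stands. A reader might infer that no planned test matches the hypothesis, and the article does not support that. The match is incomplete, because the interaction is omnibus, non-directional and not named as primary. Nor does the hypothesis need rewording to become a between-condition claim, since it already compares CFT with CBT.

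A reader might also infer that the planned false-positive rate is nearly doubled. The article does not support that either. The 9–10% figures arise only if the condition main effect, or either single time point, also counts as success. The article says neither, and its *and*, read literally, requires both time points. Misreading the time effect as efficacy is likewise a risk and not something the article does.

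A third reply is that an article may leave follow-up contrasts to a fuller document. That would excuse silence. Here the article states its analysis and its effect sizes, and what it states does not deliver the comparison that it hypothesizes.

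Finally, the trial is described as testing preliminary efficacy. That lowers the stakes, but the hypothesis is still framed in terms of significance, with 80% power at alpha .05.

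**Conclusion.** The concern holds in a limited form. The stated analysis contains a test related to the primary hypothesis, but it neither designates that test as primary nor estimates the CFT–CBT difference at the two named times. A significant interaction would not confirm the hypothesis: under a post-intervention-only effect of 0.85 SD it occurs in about 87% of trials at N = 50, while the two-time-point claim is supported in 2–3%. If both time points are required, as the wording reads, the power of about 87% at N = 50 for the interaction does not carry over to change-score contrasts, where it is about 74%.

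The power figures rest on rho = 0.5, equal variances, equal arms and complete data. The equality of the interaction's power under the lasting and post-only patterns does not depend on the value of rho within that model. The conclusion concerns fit to the hypothesis and not type I error inflation.

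**What to change.** Make the primary analysis the baseline-adjusted CFT–CBT difference in BDI-II, estimated at post-intervention and at 3 months, each with a 95% confidence interval. Then state one of two rules:

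- Both differences must be significant at two-sided 5%, which is the literal reading of the hypothesis and needs no alpha adjustment.
- Post-intervention is tested first at two-sided 5%, and 3 months only if the first is significant.

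State that the time and condition main effects are descriptive. Report between-arm effect sizes with 95% confidence intervals beside the within-condition ones.

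The data are already planned, so the cost is wording, a registry update and a little more analysis. The downside is that an effect at only one time point would not fully confirm the hypothesis, and under the fixed sequence an effect seen only at 3 months could not be claimed formally.

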## Method

### Participants and recruitment

Potential participants will respond to advertisements on social media for a free depression intervention for young LGB men and women aged 18–25 years. Recruitment will be nationwide around Australia, and advertisements will direct individuals to a brief survey. The survey will provide further information about the study as well as invite potential participants to provide their contact details and complete a brief screening questionnaire to assess their eligibility. Advertisements will be targeted to meet the following criteria for gay and bisexual male participants: Gender = male; romantic interest = male or male and female; aged 18–25; residing within Australia. Advertisements will be targeted to meet the following criteria for lesbian and bisexual female participants: Gender = female; romantic interest = female or female and male; aged 18–25; residing within Australia. The brief screening questionnaire consists of the Beck Depression Inventory-II [28], the Suicide Behaviour Questionnaire [29]; and key demographic information including age, gender, sexual orientation, ethnicity, whether participants are currently taking medication for depression, and whether they are currently engaged in another form of psychological therapy for their depression.

Participants will be included in the study if they meet the following inclusion criteria: (1) aged 18–25 years; (2) currently experiencing clinically significant depressive symptomatology, as evidenced by BDI-II scores of 13 and above; (3) and identify as gay, bisexual, lesbian, or non-heterosexual. Participants will be excluded from participating if they meet the following exclusion criteria: (1) currently receiving individual psychological intervention; (2) currently at *imminent* risk of harm to themselves, including planning or intending to engage in suicidal and/or para-suicidal behaviors. The presence of suicidal ideation is not an exclusion criteria. No other inclusion or exclusion criteria were used to assess eligibility for participation.

Following participants’ expressions of interest and completion of the screening questionnaire, a research assistant will assess eligibility based on the above criteria, and will contact potential participants to provide further details about the project. Specifically, the research assistant will outline that participants will be randomly assigned to one of two treatment conditions, answer questions, and provide potential participants with a consent form and the pre-assessment questionnaire. Ineligible participants will be referred to other services as appropriate.

